## Data collection and statistical analysis

A detailed statistical analysis plan will be prepared. A blind review of the data will be performed after the end of the planned follow-up period without looking at the randomised treatment for each trial participant. Attritions will be excluded from the analysis. Intention-to-treat principle will be used for the analysis. Results will be expressed in proportion and means (±SD) for categorical and continuous variables, respectively. Student's t-test will be used to compare CCTs between the study groups. A repeated measures analysis of variance will be conducted to assess for any difference in CCT between bevel-up and bevel-down groups over time. All the data will be analysed using SPSS V.16.

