### Postoperative evaluation

All the patients will be put on topical ciprofloxacin and dexamethasone eye drops combination, one drop six times a day for 1 week for the first week, after which it will be gradually tapered over a period of 1 month. All the patients will be examined postoperatively on day 1, day 7 and at the end of 1 month. The examinations will include UDVA, CDVA, slit lamp biomicroscopy, applanation tonometry, funduscopy and CCT measurement. Telephonic reminders will be made to encourage the complete follow-up.

*Outcome measure*: The CCT will be measured on days 1, 7 and 30. Deturgescence of the corneal stroma is controlled by the pumping action of the endothelial layer and can be monitored by the measurement of CCT. Loss or damage of endothelial cells leads to an increase in corneal thickness, which may ultimately induce corneal decompensation and loss of vision.^13^ A significant linear correlation exists between increase in corneal thickness in the immediate postoperative period and percentage of endothelial cell loss.^14^ Hence, CCT measurement can be used as a simple tool to assess the amount of corneal endothelial damage postcataract surgery.

Figure 1 shows the proposed flow of the participants in this trial.

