**Figure 1 BMJOPEN2016012024F1:**
[figure not shown]
Flow diagram of the trial participants. ACD, anterior chamber depth.

*Sample size calculation*: The sample size calculation is based on the anticipated differences in the CCT (mean±SD) between the two groups. A sample of 50 in each group is needed to detect a mean CCT difference of 20 µm with an SD of 35.3,^15^ 1:1 allocation ratio, α error of 0.05 and a power of 80%.^16^ The final sample is inflated to 55 with due consideration of 10% attrition.

*Sensitivity analysis of sample size calculation for CCT*: The power of the study will be estimated based on the actual number of the study participants who complete the study and the observed differences in CCT across the two study groups.

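### The plan excludes drop-outs and in the next sentence claims intention-to-treat; the result is a completer analysis under an ITT label, and the post-randomisation surgical exclusions widen the conflict

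*Protocol article*

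**What the plan says.** The section on data collection and statistical analysis states: "Attritions will be excluded from the analysis. Intention-to-treat principle will be used for the analysis". It then gives two analyses of CCT. The first is cross-sectional: "Student's t-test will be used to compare CCTs between the study groups". The second is longitudinal: "A repeated measures analysis of variance will be conducted to assess for any difference in CCT between bevel-up and bevel-down groups over time". The outcome schedule under Postoperative evaluation is: "The CCT will be measured on days 1, 7 and 30".

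Three other places bear on who is analysed:

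- The sample size paragraph arrives at 50 per group and raises this to 55 for 10% attrition. The sensitivity paragraph after it bases the later power estimate on participants who finish the study.
- The exclusion criteria under Participants and methods remove cases with intraoperative complications and cases in which direct chop proved impossible.
- The abstract places randomisation before surgery.

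The article does not define attrition, does not say what it means by intention-to-treat, and gives no rule for missing CCT other than exclusion. It announces a detailed analysis plan, which is not shown.

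**The concern.** Intention-to-treat keeps randomised patients in the analysis in their allocated arm. A rule that removes everyone lost to follow-up leaves a set defined by what happened after allocation. Two analysts following this section could analyse different patients, and both could claim compliance.

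Three things are at stake:

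- **Bias.** If loss is related to the state of the cornea or to vision, and differs by arm, the comparison of completers no longer rests on randomisation alone. The surgical exclusions carry the same risk more directly, since a complication or a failed chop may depend on how the tip is held.
- **Avoidable data loss.** CCT already measured on days 1 and 7 can be discarded because day 30 is missing.
- **Labelling.** The result would be published as ITT although it is not.

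**Working it through.** **1. The rules side by side.**

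| Place | Rule | Set it implies |
|---|---|---|
| Statistical analysis | "Attritions will be excluded from the analysis" | completers |
| Statistical analysis, next sentence | "Intention-to-treat principle will be used for the analysis" | all randomised, as allocated |
| Sensitivity analysis of sample size | power from those who finish | completers |
| Exclusion criteria | intraoperative complication or no direct chop | randomised patients with uneventful surgery |

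Three of the four rows define the set by events after allocation. Only the second does not.

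**2. Reproducing the sample size.** The inputs come from the sample size paragraph: "A sample of 50 in each group is needed to detect a mean CCT difference of 20 µm", "with an SD of 35.3", α = 0.05, power 80%, 1:1 allocation. Sidedness is not stated. Two-sided reproduces the figure; one-sided would give 39.

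n per group = 2 × (1.96 + 0.8416)² × (35.3/20)² = 2 × 7.849 × 3.115 = 48.9, so 49 by the normal approximation. By the noncentral t distribution, power is 79.3% at 49 and 80.1% at 50, so 50 is confirmed. The inflation is 50 × 1.10 = 55.

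**3. Power when drop-outs are excluded.** At 10% attrition, 55 × 0.90 = 49.5 per group. Two-group t-test power (noncentral t, d = 20/35.3 = 0.567) is 83.8% at 55 and 79.7% at 49.5. The inflation was meant to absorb this loss, so power stays at about the planned 80%. If every drop-out occurred after day 1, keeping the observed values would leave 55 per group for the day 1 comparison, a gain of 83.8 − 79.7 = 4.1 points. That is the upper limit of the gain.

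**4. Listwise deletion in the repeated-measures ANOVA.** This is a property of the classical method, not a statement in the article. If each of the three visits is missed independently with probability p (assumed), the number with all three is 55 × (1 − p)³:

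| p | Complete per group | t-test power at that n (rounded down) |
|---|---|---|
| 2% | 55 × 0.941 = 51.8 | 80.9% (n = 51) |
| 5% | 55 × 0.857 = 47.2 | 77.6% (n = 47) |
| 10% | 55 × 0.729 = 40.1 | 70.6% (n = 40) |

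The last column is the power of a two-group t-test at that n, used as a scale; it is not the power of the ANOVA.

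**5. Scale of possible bias.** The documents give no figures for this, so the inputs are assumed. Let q be the excess share excluded in one arm and D the mean CCT difference between excluded and retained eyes. The between-group difference then shifts by q × D.

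- Low end: 0.05 × 20 = 1.0 µm, which is 1.0/20 = 5% of the target difference.
- High end: 0.15 × 70.6 (two SDs) = 10.6 µm, which is 10.6/20 = 53% of the target.

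**The case against.** **Attrition is undefined and the label can be read charitably.** ITT might mean only that patients are analysed in their assigned arm among those with data. That reading is possible, but it describes an available-case or completer analysis, which should be named as such. It is fair to say that losing the day 1 and day 7 values of someone who misses day 30 is an inference; the sample-size section's reference to completers supports it without proving it. Nor can any practical analysis include a patient with no postoperative CCT unless values are imputed, so the point is about the stated rule and its label.

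**The analysis plan may settle it.** Covariance structure and imputation details do belong there. But the article has already fixed both an exclusion rule and a label, and a later plan cannot follow both.

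**The harm may be small.** Follow-up is one month at one hospital with telephone reminders, the trial calls itself exploratory, and nothing says that loss tracks corneal state. This stands: bias is possible, not shown.

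**A stronger reading is not supported.** A reader might infer that the ANOVA dilutes an early effect the trial was sized to find, or that the attrition rule leaves the trial underpowered. On the first, the sample size paragraph names no visit for the 20 µm, and a difference over time is most naturally the group-by-time interaction. Take an assumed scenario of 50 per arm, SD 35.3, within-patient correlation 0.7 and effects of 20, 10 and 3 µm at days 1, 7 and 30. The group main effect has only about 26% power with baseline as a level and 40% without, but the interaction has about 92% and 80%, against 80% for a day 1 t-test. With a constant 20 µm at all three visits, the main effect without baseline has about 88%. The dilution argument therefore depends on the chosen term and effect pattern. On the second, step 3 of the working shows that the loss is already budgeted.

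**Conclusion.** The contradiction stands, and it rests on the current text alone. As written, the plan yields a completer analysis called ITT, further narrowed by exclusions that arise during surgery after allocation. It governs who enters every CCT comparison, so it should be corrected before unblinding.

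Its size in power is small: about 80% at the planned attrition, with at most 4 points to recover. Its size in bias cannot be computed from the documents; the range of 1.0 to 10.6 µm rests entirely on the assumed differential exclusion and eye-to-eye difference. The finding makes no claim that the sample size is wrong or that the ANOVA would miss the effect.

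**What to change.** 1. Delete the sentence excluding attritions. Define the main analysis set as all randomised patients with any postoperative CCT, in the arm to which they were allocated.
2. Reconcile the exclusions for intraoperative complications and for failed direct chop with that set. State whether such patients remain in the main analysis once randomised; without this, deleting the attrition sentence does not restore ITT.
3. Replace the repeated-measures ANOVA with a mixed model for repeated measures (arm, visit, arm × visit and baseline CCT). It keeps patients with partial data and gives the arm contrast at each visit.
4. Add one sensitivity analysis for missing values, for example multiple imputation with a shift applied to the imputed values.
5. If drop-outs are still to be excluded, call the analysis complete-case and drop the ITT label.

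The cost is a few sentences of wording and slightly more analysis work. No visit or measurement changes for patients followed as planned.

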### Data monitoring committee

An independent data monitoring committee (DMC) will be established. The DMC will monitor the course of the trial and if necessary will give a recommendation to the main investigator of the trial for discontinuation, modification or continuation of the study and the same shall be communicated to the University's Ethics Committee and Clinical Trial Registry of India.

### Safety parameters

All the adverse events will be listed and displayed in summary tables. The total number of adverse events, the minimum, maximum and mean number of adverse events per patient will be reported.

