**Methods and analysis:**

This is a prospective, triple-blinded (trial participant, outcome assessor and the data analyst), randomised controlled trial with 2 parallel groups and with an allocation ratio of 1:1. It will be conducted in a tertiary care hospital, Mangaluru, India. The objective is to compare the postoperative central corneal thickness changes between the bevel-up and bevel-down techniques of phacoemulsification. Patients aged >18 years with immature cataract undergoing phacoemulsification will be selected for the study. The important exclusion criteria are the history of previous significant ocular trauma or intraocular surgery, corneal pathology, pseudoexfoliation syndrome, intraocular inflammation, a preoperative fully dilated pupil <6 mm, anterior chamber depth <2.5 mm and nuclear sclerosis grade >4. After randomisation, patients will undergo phacoemulsification surgery either by a bevel-up or bevel-down procedure. With an estimated power of 80%, the calculated sample size is 55 patients in each group. The recruitment will start from April 2016.

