Several phacoemulsification techniques have been developed and modified.^3–7^ Although many techniques have been proposed, the risks of posterior capsular rupture and corneal endothelium damage persist. In theory, damage to the corneal endothelium is minimised by delivering the lowest phaco energy only in the direction necessary to emulsify the lens nucleus. Furthermore, phacoemulsification should occur in the posterior chamber rather than in the iris plane or the anterior chamber.^8^ Hence, it has traditionally been believed that the bevel of the needle should be turned towards the nucleus or the nuclear fragment (ie, bevel-down).^9^ However, Faramarzi *et al*^10^ hypothesise that in the bevel-up technique, the phaco tip, and therefore the source of heat, are farther from the endothelial cells than in the bevel-down technique and this decreases the chance of endothelial cell damage. Further another clinical trial by Raskin *et al*^11^ concluded in their study that bevel-up tip position has a negative effect on corneal endothelial cells compared with the bevel-down position. Hence, there is a difference of opinion among ophthalmologists with respect to the phaco tip position during phacoemulsification. This subject has not been extensively studied earlier, hence this study is planned.

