### Participants and methods

*Inclusion criteria*: Consecutive patients aged >18 years with immature cataract undergoing phacoemulsification at Yenepoya Medical College Hospital, Mangaluru, India will be selected for the study.

*Exclusion criteria*: History of previous significant ocular trauma or intraocular surgery, corneal pathology, pseudoexfoliation syndrome, intraocular inflammation, a preoperative fully dilated pupil smaller than 6 mm, anterior chamber depth (ACD) <2.5 mm and nuclear sclerosis grade >4. Cases with intraoperative complications, those where direct chop could not be done and patients not willing to participate in the study will be excluded.

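### Eyes with intraoperative complications or failed direct chop are excluded after randomisation, and the stated safety summaries do not ensure that the patients affected are counted by arm

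*Protocol article*

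**What the plan says.** The last sentence of the exclusion criteria (Protocol article, Participants and methods) reads "Cases with intraoperative complications, those where direct chop could not be done and patients not willing to participate in the study will be excluded". The abstract (Methods and analysis) fixes the order of events: "After randomisation, patients will undergo phacoemulsification surgery either by a bevel-up or bevel-down procedure". The Interventions section says the tip is held in the allocated position whenever it is in the anterior chamber.

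The section on data collection and statistical analysis declares the intention-to-treat principle, removes attritions from the analysis, and announces a detailed analysis plan. It also states that "Student's t-test will be used to compare CCTs between the study groups".

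On harms, the Introduction says that "the risks of posterior capsular rupture and corneal endothelium damage persist". The second of these is what the outcome is meant to capture: "CCT measurement can be used as a simple tool to assess the amount of corneal endothelial damage postcataract surgery" (Postoperative evaluation). The section Safety parameters has two sentences: "All the adverse events will be listed and displayed in summary tables", and "The total number of adverse events, the minimum, maximum and mean number of adverse events per patient will be reported".

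**The concern.** Two of the listed exclusions are not eligibility criteria in the usual sense. Nobody can know before the operation that a complication will occur or that direct chop will fail. By then the patient has been randomised, and for any problem arising in the phacoemulsification step the allocated bevel position is already in use. The exclusion can therefore be a consequence of treatment. The surgeon, who is not among those blinded, is also the person placed to judge that direct chop could not be done.

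Two things are at stake. First, corneal thickness would be compared between two selected groups of uncomplicated eyes, no longer the randomised groups. A technique that caused more complications would lose those eyes, and its remaining eyes could look better for that reason. Second, the protocol does not secure a count of posterior capsular rupture by arm on all randomised patients. The summaries it commits to do not repair this: a total and a mean per patient give a rupture and a trivial event the same weight, and neither says how many patients were affected.

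**Working it through.** **1. The passages side by side**
- Exclusion criteria: complicated eyes and failed chops are out.
- Abstract: surgery follows randomisation. Failure of direct chop needs the phaco tip in the eye, so that exclusion must come after allocation.
- Analysis section: intention to treat. A randomised, operated patient removed for an intraoperative event is not analysed by intention to treat, so these statements cannot both be followed.
- Safety parameters: all adverse events are listed, but no population is named. Whether an excluded eye is in the listing is left open.
- Named risks: endothelial damage is compared between arms through CCT. Posterior capsular rupture is an intraoperative complication and falls under the exclusion.

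**2. The plan's own sample size**

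Inputs (Sample size calculation): difference 20 µm, SD 35.3, α 0.05 (two-sided assumed), power 80%, 1:1.

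n = 2 × [35.3 × (1.960 + 0.842) / 20]² ≈ 48.9, so 49 per arm. The t-test version gives 49.9, so 50 as stated. 50 × 1.10 = 55 as stated. The figure reproduces and is not in dispute.

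**3. What the exclusion costs in CCT power**

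Exclusion rates are assumed. With 10% attrition, 55 × 0.90 = 49.5 per arm remain. Removing a further 0%, 2%, 5% or 10% leaves 49.5, 48.5, 47.0 or 44.6, and power is about 80%, 80%, 78% or 76%. The loss is small. The problem is selection, not lost precision.

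**4. How many complications to expect**

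The documents give no rates, so a range is assumed. Expected cases per arm = 55 × rate: at 1%, 2%, 5% and 10% this is 0.6, 1.1, 2.8 and 5.5. If an arm has none, the exact two-sided 95% upper limit is 1 − 0.025^(1/55) = 6.5%.

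**5. An illustration with assumed counts, 5/55 v 1/55**
- Proportions: 5/55 = 9.1%, 1/55 = 1.8%; difference 7.3 percentage points.
- Exact (Clopper-Pearson) 95% intervals: 3.0% to 20.0% and 0.05% to 9.7%.
- Fisher's exact test, 6 events in 110 patients: P(5 in one given arm) = C(55,5) × C(55,1) / C(110,6) = 0.0893; P(6) = C(55,6) / C(110,6) = 0.0135; two-sided p = 2 × (0.0893 + 0.0135) = 0.21.

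**6. Power to compare complications at 55 per arm**

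The first power column uses the normal approximation for two proportions. The second sums the binomial probabilities of all tables with Fisher p ≤ 0.05. With so few events the approximation is optimistic.

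| Assumed rates | Normal approximation | Fisher's exact test |
|---|---|---|
| 1% v 5% | 23% | 3% |
| 2% v 10% | 42% | 23% |
| 5% v 15% | 41% | 28% |
| 5% v 20% | 67% | 57% |

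Keeping every operated eye therefore supports a description by arm, not a powered test.

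**The case against.** The strongest reply is that the safety section says all adverse events will be listed. Nothing restricts that listing to analysed eyes, and the exclusion can be read as applying to the corneal thickness comparison only. This stands in part. A reader might infer that complicated eyes will appear as 0 v 0 in the safety tables; that is a likely consequence of the word excluded, but the protocol does not state it. What remains is that the text does not settle the matter, and the conflict with intention to treat exists on either reading.

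A reader might also infer that the trial fails to compare its main harms. That goes too far: endothelial damage is assessed through CCT and compared between arms, so the gap concerns posterior capsular rupture, other intraoperative complications and failed chop. Nor can it be said that the data monitoring committee would see filtered data, since the protocol does not describe what the committee receives.

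It can fairly be said that layout by arm, event categories and analysis sets usually belong in the analysis plan, and one is announced. Their absence alone would be no finding. But the exclusion is written into the protocol's eligibility criteria, so a plan that follows the protocol would inherit it, and the safety section commits to specific summaries that do not give the proportion harmed.

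Finally, a trial of this size could seldom show that one position causes more complications. That is correct, and it limits what the remedy can claim. It is not a reason to leave the events uncounted.

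**Conclusion.** The point holds in a bounded form. The protocol excludes patients for events that occur after randomisation and may depend on the allocated technique, which contradicts its intention-to-treat statement. On the likely reading, posterior capsular rupture would not be compared on all randomised patients, and a CCT benefit could rest on uncomplicated eyes alone.

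The size cannot be fixed from the documents, because they give no complication rate. Over assumed rates of 1% to 10%, about 0.6 to 5.5 eyes per arm would be affected. The effect on CCT power is at most a few percentage points; the harm is possible bias in the CCT comparison and a missing count of complications. The conclusion assumes that some complications arise once the tip is in the eye, so that bevel position could influence them. It rests on the protocol text, without sight of the flow diagram or the announced analysis plan. The point should be corrected before analysis, and it does not call the design into question.

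**What to change.** 1. Reconcile the exclusion criteria with the intention-to-treat statement: say that intraoperative complications and failed direct chop do not remove a randomised patient from the intention-to-treat analysis. If a comparison in uncomplicated eyes is wanted, label it as supplementary.
2. Define the safety set as every randomised patient whose surgery was started.
3. Add to the safety section a by-arm table of the number and percentage of patients with at least one adverse event, with separate lines for posterior capsular rupture, other intraoperative complications and failed direct chop, each with a risk difference and exact 95% confidence interval. State that the table is descriptive.

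The total, minimum, maximum and mean per patient may stay beside it. The cost is a few sentences and one table. No new data on these events are needed, because they must be identified anyway to apply the exclusion; the patients concerned would need to stay in the planned follow-up so that their CCT is available.
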